### ****7.2.1 Patient Selection and Recruitment****

Participants will be recruited during **endocrine gynaecology consultations** at the **Jeanne de Flandre Hospital**.

### ****7.2.2 Information and Informed Consent****

Participants will receive **comprehensive oral and written information** explaining all study procedures.
An **information sheet** will be provided by the investigator or a delegated physician prior to inclusion.

**Written informed consent** must be obtained from each participant **before any protocol-specific procedures**are initiated.
The consent form will be signed by both the **investigator (or delegated physician)** and the **participant**.

The information sheet and consent form will be prepared in **three copies**:

- One copy for the participant
- One retained by the investigator
- One sent to the sponsor in a **sealed envelope**

A **reasonable reflection period (1 week)** will be provided to allow the participant to confirm or decline participation.

### ****7.2.3 Inclusion Visit****

At the inclusion visit, **written informed consent** will be collected, and the **study procedures** will be carried out over a **single study day (8:00 a.m. to 4:00 p.m.)**, scheduled **at the beginning of the menstrual cycle**.

### ****7.2.4 End-of-Study Visit****

Each participant will receive a **follow-up phone call** from **[name] 3 to 4 days after study completion**to ensure the absence of adverse effects potentially related to study participation (e.g., redness, skin warmth, itching, urticaria, nasal discharge, rapid or irregular pulse, tongue or throat swelling, sneezing, wheezing, breathing difficulties, dizziness, asthenia, or catheter site discomfort, as well as nausea or headache).

### ****7.3 Study Duration****

- **Expected recruitment period:** 12 months
- **Duration of participation for each subject:** 1 week
- **Total study duration:** 12 months and 1 week

### ****7.4 Study Procedures and Differences from Standard Care****

This is a **clinical research study** involving **one day of hospitalization** for **blood sampling every 10 minutes over 8 hours**.

This procedure does **not correspond to standard medical care**, which typically involves only a **single baseline hormonal assessment**, followed by treatment tailored to the patient’s clinical presentation — such as **ovulation induction** (for infertility), **anti-androgen therapy** (for acne, hirsutism, or alopecia), or **hormonal therapy** to induce withdrawal bleeding (for menstrual irregularities).

# INVESTIGATIONAL MEDICAL PRODUCT

### ****8.1 Name and Description of the Investigational Medicinal Product (IMP)****

**Orgalutran® 0.25 mg** (Ganirelix) will be used at doses **significantly lower** than the recommended therapeutic doses.

For this pilot study:

- **10 participants** will receive an injection corresponding to **one-quarter of the standard dose** (Experimental Group 1), and
- **10 participants** will receive an injection corresponding to **one-tenth of the standard dose** (Experimental Group 2).

The **dilution**of the investigational product will be performed by the **qualified study nurse** prior to administration.

See the **Summary of Product Characteristics (SmPC)** for Ganirelix (Annex 4).

### ****8.2 Labelling of the Investigational Medicinal Product****

The investigational product will be **labelled in accordance with Good Clinical Practice (GCP) and applicable regulatory requirements**, clearly identifying:

- The **name of the investigational product (Ganirelix)**
- The **dose and concentration after dilution**
- The **study identification code**
- The **participant identification number**
- The **administration route (subcutaneous)**
- The **storage conditions**
- The **mention “For clinical trial use only – Not for sale”**

Labelling and documentation will be managed by the **hospital pharmacy** under the supervision of the **principal investigator**.

# BIOLOGICAL ANALYSES

**Routine Clinical Tests and Study-Specific Biological Analyses**

All laboratory analyses will be conducted under the supervision of **[name] [name]**, Department of **Hormonology, Nutrition, and Oncology**, at the**Institute of Biochemistry and Molecular Biology**, within the **Biology, Pathology, and Genetics Division** of **Lille University Hospital (CHU de Lille).**

| **Parameters to be Analyzed** | **Baseline (T0)** | **Intermediate Time Points (every 10 min for 8 h)** | **Final Time Point (T0 + 8 h)** | **Use (Clinical/Research)** | **Location & Responsible Unit** |
| --- | --- | --- | --- | --- | --- |
| LH | — | 1 dry tube (1.5 mL) at each time point | — | Research | CBP Biochemistry Laboratory |
| LH, FSH, Estradiol, Total Testosterone | 1 dry tube (5 mL) | — | 1 dry tube (5 mL) | Research | CBP Biochemistry Laboratory |
| AMH | 1 dry tube (5 mL) | — | 1 dry tube (5 mL) | Research | CBP Biochemistry Laboratory |
| Androstenedione | 1 dry tube (5 mL) | — | 1 dry tube (5 mL) | Research | CBP Biochemistry Laboratory |
| **Total** | **3 dry tubes (5 mL)** | **49 dry tubes (1.5 mL)** | **3 dry tubes (5 mL)** | **Research** | **CBP Biochemistry Laboratory** |

### ****Sample Storage and Handling****

Samples will be stored for **3 months** at the **CBP Laboratory**, following the same procedure as for routine hormonal assays.

- **AMH samples** will be stored for **1 year**.
- **Other hormonal assays** will be stored for **1 week**.

All samples are collected **exclusively for the purpose of this study** and will be **destroyed after analysis**, with **no biological collection or biobank** established.

### ****Total Blood Volume Collected****

| **Type of Analysis** | **Volume (mL)** |
| --- | --- |
| Biology | 103.5 mL |
| Pharmacokinetics / Efficacy | 0 mL |
| Genotyping | 0 mL |
| **Total** | **103.5 mL** |

## ****BIOLOGICAL SAMPLE COLLECTION****

**Not applicable.**
No biological collection or long-term biobank will be constituted as part of this study.

# SAFETY EVALUATION

### ****10.1 Definitions****

**Adverse Event (AE):**
Any untoward medical occurrence in a participant enrolled in a clinical study involving human subjects, whether or not it is related to the research or to the investigational product.

**Adverse Reaction (AR):**
Any adverse event considered to be related to the research or to the investigational product.

**Serious Adverse Event or Serious Adverse Reaction (SAE/SAR):**
Any event or reaction that:

- results in death,
- is life-threatening,
- requires inpatient hospitalization or prolongation of existing hospitalization,
- results in persistent or significant disability/incapacity,
- results in a congenital anomaly or birth defect, or
- is considered medically significant by the investigator.

Certain hospitalizations do not fall under the criterion of “seriousness” when they are:

- admissions for social or administrative reasons,
- hospitalizations predefined in the protocol,
- hospitalizations for medical or surgical treatment scheduled prior to the study,
- or day-hospital admissions.

**Unexpected Adverse Reaction (UAR):**
Any adverse reaction whose nature, severity, or outcome is not consistent with the information available in the product documentation, procedures, or methods used in the study.

**New Safety Information (“Fait nouveau”):**
Any new data that may lead to a reassessment of the benefit-risk balance of the study or of the investigational product, require modifications in the use of the product, in the conduct of the study, in study-related documentation, or justify suspension, interruption, or modification of the study protocol or similar studies.

### ****10.2 Description of Safety Evaluation Parameters and Protocol-Related Risks****

**Risks Related to Treatment:**
Possible allergy to Ganirelix manifested by redness, skin warmth, itching, urticaria, nasal discharge, rapid or irregular pulse, swelling of the tongue and throat, sneezing, wheezing, severe breathing difficulties, or dizziness.
Special caution is required in women presenting with signs or symptoms of an active allergic condition or with a known history of allergic predisposition. Treatment with Ganirelix is **not recommended** for women with severe allergic disorders.

**Other risks described in the Summary of Product Characteristics (SmPC) for Orgalutran:**

- Ovarian hyperstimulation syndrome (OHSS): lower abdominal pain with nausea or vomiting, decreased urine output, weight gain, or breathing difficulties (not applicable in this study context);
- Skin irritation at the injection site: redness, itching, swelling;
- Nausea;
- Headache.

**Risks Related to Blood Sampling:**
Blood collection may cause very slight discomfort due to frequent sampling, and mild bruising may occur at the site for several days following the blood draws.

### ****10.3 Procedures for Recording and Reporting Adverse Events****

#### ****Responsibilities of the Investigator****

**Collection of Adverse Events:**
All adverse events will be recorded on the adverse event report forms included in the case report form (CRF). Each adverse event will be documented individually.

**Severity grading** will be determined as follows:

- Mild (Grade 1): no interference with daily activities;
- Moderate (Grade 2): moderate interference with daily activities but acceptable;
- Severe (Grade 3): marked interference with daily activities, unacceptable;
- Life-threatening (Grade 4);
- Death (Grade 5).

All adverse events must be **graded and assessed** for **causality and outcome**.

#### ****Reporting of Serious Adverse Events (SAEs)****

The investigator must notify the sponsor **immediately upon awareness** of any **serious adverse event** occurring during the study period, except for those explicitly listed in the protocol as **not requiring notification**.

Each SAE must be documented using the **“Serious Adverse Event” reporting form** provided in the CRF and transmitted to the sponsor’s **Clinical Trials Vigilance Unit (Direction de la Recherche et de l’Innovation, CHU Lille)** by:

- **Email:** [contact]

For each SAE, the investigator must provide detailed documentation including:

- a clear and complete description of the event (preferably as a medical diagnosis),
- severity, start and end dates, outcome,
- assessment of the causal relationship between the SAE and:
  - the investigational product and/or
  - any concomitant treatment.

Follow-up of all adverse events will be ensured by the investigator until resolution or stabilization.

Whenever possible, the investigator must attach anonymized supporting documents:

- hospitalization or hospital extension reports,
- relevant laboratory or imaging results,
- any other documentation deemed useful.

#### ****Reporting Period for Serious Adverse Events****

All SAEs must be reported if they occur:

- from the **date of signature of the informed consent**,
- throughout the participant’s study follow-up period,
- and for a **minimum of 7 days** after completion of the study procedures.

There is **no time limitation** for reporting SAEs considered likely to be related to the study or to the investigational product (e.g., delayed effects such as cancer or congenital anomalies).

#### ****Reporting of Pregnancies****

Pregnancy is **not considered a serious adverse event**, but any pregnancy occurring during the trial must be **reported immediately** using the **standard pregnancy notification form** to the sponsor.

The sponsor will ensure appropriate follow-up if deemed necessary.
The investigator must follow the participant until the **end of the pregnancy or its termination** and report the outcome using the **standard pregnancy outcome form**.

If the pregnancy outcome meets SAE criteria (e.g., spontaneous abortion with hospitalization, fetal death, congenital anomaly), the **SAE reporting procedure** must be followed.

### ****10.4 Responsibilities of the Sponsor****

#### ****Reporting of Serious and Unexpected Adverse Reactions (SUSARs)****

For each SAE, the sponsor will assess **severity**, **causality**, and **unexpectedness** with respect to the investigational product and/or concomitant treatments.

The sponsor must report all **suspected unexpected serious adverse reactions (SUSARs)** to the **ANSM** (French Medicines Agency) and the **Ethics Committee (CPP)**:

- **Immediately** (without delay) for any **fatal or life-threatening** SUSAR;
- **Within 15 days** of awareness for all **other SUSARs**.

Follow-up reports providing relevant additional safety information will be sent:

- **Within 8 days** of the initial report for fatal or life-threatening SUSARs;
- **Within 8 days** following the 15-day initial report for other SUSARs.

#### ****Reporting of New Safety Information****

In the event of **new safety information**, the sponsor will immediately notify the **CPP** and **ANSM** by email, as soon as such information becomes known, along with any measures taken in response.

#### ****Annual Safety Report****

Once per year for the duration of the study (or upon request), the sponsor will submit to the **ANSM** and the **CPP** an **annual safety report**.
This report will include a **comprehensive analysis** of the study’s safety profile, incorporating all newly available safety data.
It will include **summary tables** of all **serious adverse events and reactions** that occurred during the clinical trial.

### ****10.5 Independent Data Safety Monitoring Committee****

Given the existing knowledge regarding Ganirelix and the **low doses** used in this study population, the establishment of an **Independent Data Safety Monitoring Committee (DSMC)** is **not considered necessary**.

# DATA MANAGEMENT

The individual data collected during the study will first be recorded on a source document, then entered electronically to create a computerized database.
All data are confidential in accordance with the French Data Protection Act of January 6, 1978, and the General Data Protection Regulation (GDPR).

Data processing will be carried out in compliance with the Reference Methodology MR-001 established by the CNIL (Commission Nationale de l’Informatique et des Libertés), within the Statistical, Economic Evaluation and Data Management Unit (SEED), under the supervision of [name] at Lille University Hospital (CHU de Lille).

The data will be entered into a secure electronic database using the software Ennov Clinical, which is certified for data management in clinical trials and compliant with FDA (Food and Drug Administration) recommendations.
All data will be hosted on a secured server belonging to CHU de Lille.

This software enables the creation of an electronic case report form (eCRF) and the implementation of data validation and consistency rules, allowing automatic query generation during data entry.
Before database lock, a data manager will perform data monitoring through Ennov Clinical, based on predefined consistency rules established in collaboration with the study’s principal investigator.

Access to the data will be restricted to individuals directly involved in the study.
Data may be modified only by an investigator-physician participating in the study or by a delegated collaborator explicitly authorized to do so.

All data related to this study will be archived for a minimum of fifteen (15) years from the end of the research or its early termination, without prejudice to the applicable legal and regulatory requirements in force.

# STATISTICAL ANALYSES

**General Principles**
All statistical analyses will be performed independently by the Department of Biostatistics, University of Lille, under the supervision of [name]. Analyses will be conducted using 10.0.2 GraphPad Prism software (GraphPad; San Diego, CA, USA).

All analyses will be performed on the per-protocol population, unless otherwise specified. The level of statistical significance will be set at α = 0.05 (two-sided). No adjustment for multiple testing will be applied, and all secondary analyses will be considered exploratory. Results will be presented as effect size estimates with corresponding 95% confidence intervals (95% CI).

**Description of Data**
Baseline demographic and clinical characteristics will be described by treatment group.
Quantitative variables will be summarized as mean (standard deviation or standard error). The normality of data distributions will be evaluated using the Shapiro–Wilk test.

For normally-distributed data, data will be compared using unpaired two-sided Student’s *t*-test. For non-normally distributed values, Mann-Whitney U test will be used.

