# STUDY OBJECTIVES

### ****3.1 Primary Objective****

To assess the effect of Ganirelix on the reduction of luteinizing hormone (LH) pulse frequency, comparing two different dose levels.

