### ****5.2 Measures Taken to Minimize Bias****

Each participant will serve as her own control in this study, thereby minimizing potential bias.

The phenotypic diversity among women with PCOS — particularly regarding lean versus obese status — has a significant impact on mean plasma LH levels. To reduce variability, this pilot study will focus exclusively on **lean women with a highly uniform PCOS phenotype**, defined as follows:

- Age between **18 and 35 years**,
- **BMI below 30 kg/m²**,
- **Hyperandrogenism** (total testosterone > 0.39 ng/mL),
- **Elevated plasma LH** (> 8 IU/mL),
- **Elevated plasma AMH** (> 28 pmol/L).

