### ****7.2 Study Procedures****

This is a **phase 1 pilot study** with **two parallel groups**, evaluating the efficacy of two different doses of Ganirelix in **20 women with PCOS**, defined by **oligo-/anovulation**, **hyperandrogenism**, and **elevated circulating LH levels**.

An **intravenous cannula** will be inserted, and **blood samples will be collected every 10 minutes** for a **4-hour baseline period** starting at 8:00 a.m.
Subsequently, Ganirelix will be administered as a **single subcutaneous injection** at one of two doses:

- **0.025 mg** (n = 10 PCOS patients)
- **0.0625 mg** (n = 10 PCOS patients)

These doses correspond to approximately **one-tenth and one-quarter** of the standard clinical dose used in **IVF protocols** to achieve full LH suppression.

Following Ganirelix administration, blood sampling will continue every 10 minutes for an additional **4-hour period**.

The **primary endpoints** include mean LH levels, as well as LH pulse **frequency and amplitude**, evaluated before and during treatment with Ganirelix.
In healthy women, LH surges occur approximately every 90 minutes during the early follicular phase, whereas **lean women with PCOS** may exhibit **one or more LH pulses per hour**.

The expected outcome is to determine the Ganirelix dose that reduces the **abnormally elevated frequency** of LH pulses by approximately **20–30%**, bringing them closer to normal physiological values.

**Secondary outcomes** include reproductive hormone markers — **serum testosterone, androstenedione, LH, FSH, estradiol, and AMH levels** — measured before treatment and **4 hours post-injection**.

The **pretreatment period** (baseline LH secretion and pulsatility) will be compared to the **4-hour post-antagonist period.**An **LH pulse** will be defined as a **≥20% incremental change** in LH concentration between the nadir and the subsequent peak, as previously described in similar clinical studies (Ref. 25).

The degree of gonadotropin suppression will be calculated as a **percentage of inhibition** relative to the pre-antagonist period:

$$\text{Inhibition (\%)}=\frac{(\text{PRE mean}-\text{nadir})}{\text{PRE mean}}\times100$$

as described previously (Ref. 26).
Hormone nadir levels will be computed using a **moving average**.
For LH, a **6-point moving average** (equivalent to 1 hour of sampling) will be used, as the nadir is expected to occur within the 10-minute sampling intervals.

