**Secondary Endpoint Analyses**
- LH variation (mean, basal and total LH) before and after Ganirelix injection will be assessed.
- Androgen production variation will be evaluated as the difference in total testosterone and androstenedione levels between H8 and H0 (4 hours post- vs. pre-injection).
- FSH, estradiol, and AMH concentrations will be compared between H0 and H8 to assess hormonal changes after treatment.

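### The only tests named are for independent samples, yet the efficacy endpoints are before/after contrasts within the same woman

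*Protocol*

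**What the plan says.** Under Statistical Analyses, Description of Data, and again in the synopsis row on the statistical analysis plan, the protocol gives one rule for comparisons: "For normally-distributed data, data will be compared using unpaired two-sided Student"'s t-test, and "For non-normally distributed values, Mann-Whitney U test will be used". The Primary Endpoint Analysis paragraph covers only how pulse frequency is determined and names no test. The Secondary Endpoint Analyses paragraph names none either. General Principles sets a two-sided 5% level and promises effect estimates with 95% confidence intervals.

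The design sections describe within-woman comparisons:

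- Section 5.2: "Each participant will serve as her own control in this study, thereby minimizing potential bias".
- Section 4.1: the primary endpoint is the fall in LH pulse frequency from before to after the injection, expected to be 20–30%.
- Section 4.2: mean, basal and total LH before and after injection, and H8-minus-H0 differences for the other hormones.
- Section 7.2: the pretreatment period is compared with the four hours after the antagonist.
- Secondary Endpoint Analyses: "FSH, estradiol, and AMH concentrations will be compared between H0 and H8 to assess hormonal changes after treatment".

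The primary objective (section 3.1) also speaks of "comparing two different dose levels". There are 10 women per dose (section 5.3), assigned in order of entry and not at random (section 5.2.1).

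**The concern.** The before and after values come from the same 10 women. An independent-samples test treats them as 20 different women, so differences between women go into the standard error. Pairing exists to remove that variation. If a woman's two values are positively correlated, the unpaired test rejects too rarely, its interval is too wide, and a real fall is more easily reported as unclear.

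This also affects the trial's stated purpose. The protocol justifies its size by estimation and by supplying variability figures for a later trial. A later own-control trial needs the within-woman SD of the change, which an unpaired analysis does not produce.

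**Working it through.** **Is there a stated figure to reproduce?** No. The protocol says that no power calculation was done. Only 10 + 10 = 20 can be checked, and it agrees.

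**Inputs from the protocol:** n = 10 per dose (section 5.3); two-sided 5% level (General Principles); about one pulse per hour in lean women with PCOS (section 7.2), so about 4 pulses per 4-hour window; expected fall 20–30% (section 4.1).

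**Assumptions not in the protocol:** the pre/post correlation rho, shown over a range; equal SDs before and after; a pulse-count SD of 1.2. A 30% fall is 0.30 × 4 = 1.2 pulses, so it equals 1 SD under that assumption.

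**Standard error.** With SD σ at each time:

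- True variance of the mean change: 2σ²(1 − rho)/n.
- Variance used by the unpaired test: 2σ²/n.
- The unpaired standard error is therefore off by a factor 1/√(1 − rho): 1.20, 1.41, 1.83 and 2.24 at rho 0.3, 0.5, 0.7 and 0.8.

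**95% interval half-width, in units of σ:**

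- Unpaired: t(18) × √(2/10) = 2.101 × 0.447 = 0.94 at any rho.
- Paired: t(9) × √(2(1 − rho)/10). At rho 0.3 this is 2.262 × 0.374 = 0.85; at 0.8 it is 2.262 × 0.200 = 0.45.

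**Type I error and power.** Simulated bivariate normal values, n = 10, 200,000 trials per setting. The last two columns repeat the 1-SD power with values rounded to whole pulses (mean 4, SD 1.2).

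| rho | Type I, unpaired | Type I, paired | Half-width, unpaired / paired | Power 1 SD, unpaired | Power 1 SD, paired | Whole pulses, unpaired | Whole pulses, paired |
|---|---|---|---|---|---|---|---|
| 0.3 | 2.3% | 5% | 0.94 / 0.85 | 58% | 67% | 55% | 63% |
| 0.5 | 1.0% | 5% | 0.94 / 0.72 | 59% | 80% | 55% | 76% |
| 0.7 | 0.2% | 5% | 0.94 / 0.55 | 61% | 95% | 57% | 91% |
| 0.8 | 0.06% | 5% | 0.94 / 0.45 | 62% | 99% | 58% | 97% |

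**Smaller effect.** For a fall of 0.5 SD, power is 12% unpaired against 29% paired at rho 0.5, and 9% against 45% at rho 0.7.

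**Rank tests** (3,000 trials, continuous values). For a 1-SD fall, Mann-Whitney against Wilcoxon signed-rank gives 53% against 78% at rho 0.5, and 56% against 99% at rho 0.8. Switching to the named non-parametric test therefore does not help.

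**Where the harm vanishes or reverses.** At rho 0 the unpaired level is correct (5.0%), and its 1-SD power is slightly higher, 56% against 52%. At rho 0.1 the powers are within about one point of each other. At rho −0.2 the unpaired test rejects too often (6.9%).

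**Dose against dose.** An unpaired t-test on each woman's change, 10 against 10, has a simulated type I error of 5.1–5.2% at rho 0, 0.5 and 0.8. It is valid.

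**The case against.** **The sentence may not be meant for before/after data.** It stands under Description of Data, after baseline characteristics by group, and the primary objective compares two doses. An unpaired test of each woman's change between doses is correct. This stands in part: the misuse is inferred, not stated. But the text does not limit the rule to doses or baseline, and the analysis paragraphs offer no other test. If it was meant only for doses, the before/after contrasts have no test and the wording still needs changing.

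**A separate analysis plan may settle it.** That would answer an omission. Here the protocol names a class of test, twice, that does not fit its own design. A later plan would either inherit that or contradict it.

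**The study is an exploratory pilot.** True, and it lowers the weight of any single p-value. The promised intervals and variability estimates are still affected.

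**The correlation may be low.** Entry is restricted to a uniform phenotype and a count of about 4 is coarse, so rho for pulse counts could be small. This stands, and the size of the harm is therefore conditional.

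A reader might also infer three stronger points that the documents do not support:

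- *The dose comparison ignores baseline.* Where the endpoint is a change, baseline is already subtracted. Against change scores, baseline adjustment leaves (1 − rho²)/(2(1 − rho)) = (1 + rho)/2 of the variance: 75%, 85% and 90% at rho 0.5, 0.7 and 0.8. That is a modest gain, not the correction of an error.
- *The Shapiro-Wilk check mostly detects rounding of the counts.* For ten rounded counts it rejects about 31% of the time at the SD of 1.2 used here. Rates of 47–72% need an SD of 1.0 to 0.8.
- *The reported p-values and intervals are bound to be wrong.* That holds only if the tests are applied to pre versus post values and rho is not zero.

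**Conclusion.** The point holds in conditional form. The protocol names only independent-samples tests for a design whose efficacy endpoints are within-woman changes, and it offers no alternative for the primary or secondary analyses. Applied to pre versus post values, those tests do not keep the 5% level unless rho is zero.

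At moderate to high rho the loss is large: at 0.7, a 1-SD fall is detected 61% of the time instead of 95%, and the interval is 0.94/0.55 = 1.7 times as wide as it need be. At 0.3 the loss is about 9 points of power; near zero there is none. These sizes rest on the assumed rho, on equal SDs and, for pulse counts, on an assumed SD of 1.2. It does not follow that a true 20–30% fall will be missed, only that the chance of missing it is higher than the design requires when rho is clearly positive.

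**What to change.** Reword Description of Data and the matching synopsis row, and assign a test to each contrast:

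- **Before/after, within each dose, hormone concentrations:** paired t-test on each woman's post-minus-pre change with its 95% interval, on the log scale where suitable.
- **Before/after, within each dose, pulse counts:** name in advance an exact Wilcoxon signed-rank test that allows for ties. State the estimate of change and its interval method (for example Hodges-Lehmann), because the test alone does not give the promised interval.
- **Dose against dose:** keep the unpaired test, applied to each woman's change and labelled exploratory because allocation is sequential. Baseline-adjusted analysis is optional; without randomisation it can answer a slightly different question from the change score.
- **Reporting:** give the within-woman SD of the change and the pre/post correlation, which a later trial will need.

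The cost is wording only: no new data, participants or procedures.

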# METHODOLOGY

### ****5.1 Study Design****

This is a **single-center, phase I pilot study** with **two parallel groups**.

The study will be proposed during endocrinological gynecology consultations to all patients meeting the inclusion criteria. After obtaining written informed consent, participants will be assigned to one of the two dose groups.

During the 4 hours preceding Ganirelix injection*, baseline LH secretion and pulsatility, as well as baseline levels of androgens, FSH, estradiol, and AMH, will be measured.

Subsequently, patients will receive a **low-dose injection of Ganirelix***. LH secretion and pulsatility will be monitored for **4 hours following the injection**, along with measurements of androgens, FSH, estradiol, and AMH at **H8**.

The expected outcome is to identify the Ganirelix* dose that reduces the abnormal frequency of LH pulses in women with PCOS to values comparable to normal conditions (approximately a 30% reduction).

As **secondary outcomes**, reproductive markers (serum levels of testosterone, androstenedione, LH, FSH, estradiol, and AMH) as well as glucose, insulin, and liver function parameters will be assessed before and after the 4-hour GnRH antagonist treatment period.

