#### ****5.2.1 Randomization****

No formal randomization will be performed, as it is not considered relevant given the small sample size required.

The **first 10 patients** will receive a Ganirelix dose of 0.025 mg*, and the **next 10 patients** will receive a Ganirelix dose of 0.0625 mg*.

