**Primary Endpoint Analysis**
The primary endpoint is the reduction in LH pulse frequency during the 4-hour period following Ganirelix administration.
Analysis will include:
- Determination of LH pulse frequency using the method described above (1.1.2).

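### The only comparative tests named are unpaired and carry no baseline covariate, so the dose contrast on LH pulse frequency may be estimated less precisely than the collected data allow

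*Protocol*

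**What the plan says.** - **Objective.** Protocol section 3.1 concerns the "reduction of luteinizing hormone (LH) pulse frequency, comparing two different dose levels".
- **Tests.** Under Description of Data in the Statistical Analyses section, normally distributed "data will be compared using unpaired two-sided Student’s" t-test, and "For non-normally distributed values, Mann-Whitney U test will be used". The synopsis row on the statistical analysis plan repeats this. Neither place says which contrast the tests serve.
- **Primary analysis.** "The primary endpoint is the reduction in LH pulse frequency during the 4-hour period following Ganirelix administration". The text then covers only how pulses are determined. It gives no test, model or covariate.
- **Baseline data.** Section 5.1 says that before the injection "baseline LH secretion and pulsatility, as well as baseline levels of androgens, FSH, estradiol, and AMH, will be measured".
- **Allocation.** Section 5.2.1: "No formal randomization will be performed". The first ten women receive one dose and the next ten the other.
- **Output.** The General Principles call for effect estimates with 95% confidence intervals. The study is declared exploratory, has no power calculation, and is meant to inform a later trial.

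**The concern.** An unpaired t-test or Mann-Whitney test suits two independent groups, and the only independent groups here are the two doses. Applied to each woman's reduction, such a test subtracts her whole baseline count. At about one pulse per hour (section 7.2) that count is about 4 in 4 hours, and a count that small is noisy. Unless pre and post counts are strongly correlated, subtracting it adds more noise than it needs to. A regression on the baseline lets the data set the weight.

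What is at stake is the width of the interval for the dose contrast. The study relies on that estimate to identify a dose and to plan a confirmatory trial. The same applies to mean, basal and total LH, and to the hormones measured at H0 and H8.

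**Working it through.** The Protocol gives no SD, no pre/post correlation and no power, so there is no stated figure to reproduce.

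**Inputs from the Protocol.** n = 10 per dose; two-sided alpha 0.05; expected fall of 20–30% (section 4.1); one or more pulses per hour in lean women with PCOS (section 7.2), taken as 4 pulses in 4 hours.

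**Assumptions.** SD of a 4-hour count σ = 1 pulse, equal before and after; correlation ρ = 0.3, 0.5 or 0.7; approximate normality.

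**Dose differences.**
- 30% against 20% reduction: (0.30 − 0.20) × 4 = 0.4 pulses.
- Full 30% against no effect: 0.30 × 4 = 1.2 pulses.

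**Variance of the dose contrast.**
- Change score: (2σ²/n) × 2(1 − ρ).
- ANCOVA: (2σ²/n) × (1 − ρ²) × (1 + 1/16). The last factor is the cost of estimating the slope with 20 women.
- Ratio, ANCOVA to change score: (1 + ρ)/2 × 1.0625, which gives 0.69, 0.80 and 0.90 at ρ = 0.3, 0.5 and 0.7.

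**Power.** For the change score, noncentral t on 18 df with noncentrality δ/√(0.2 × 2(1 − ρ)). For δ = 1.2 this is 1.2/√0.28 = 2.27, 1.2/√0.20 = 2.68 and 1.2/√0.12 = 3.46. ANCOVA power is by simulation (17 df).

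| ρ | 95% CI half-width, change / ANCOVA (pulses) | Power, 1.2 pulses | Power, 0.4 pulses |
|---|---|---|---|
| 0.3 | 1.11 / 0.93 | 57% / 73% | 11% / 14% |
| 0.5 | 0.94 / 0.84 | 72% / 81% | 14% / 16% |
| 0.7 | 0.73 / 0.69 | 91% / 93% | 19% / 21% |

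**Bias from baseline differences between the groups.** Two cases behave in opposite ways.
- *Chance imbalance of 1 pulse in the observed baseline.* The change score shifts by ρ − 1, that is −0.7, −0.5 and −0.3 pulses. ANCOVA shifts by 0 under a linear model.
- *True difference of 1 pulse in stable frequency, no dose effect.* The post means differ by 1 and so do the pre means, so the change score is unbiased. ANCOVA subtracts only ρ × 1 and is left with 1 − ρ, that is 0.7, 0.5 and 0.3 pulses. Simulated type I error is about 5% for the change score and 27%, 19% and 12% for ANCOVA.

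**The case against.** **The sentence on tests is generic.** It stands under Description of Data, and the primary analysis text names no test. A reader might infer that the Protocol commits to an unpaired comparison of post-injection counts that ignores baseline. The documents do not support this. The endpoint is a reduction, section 4.1 frames it before against after, and section 5.2 makes each woman her own control. So the fair comparator is the change score, as used above, and the larger gains over a post-only test should not be claimed.

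**Adjustment is not a cure for non-random groups.** A reader might also infer that ANCOVA would remove baseline differences between the consecutive groups. It would do so for chance imbalance. With dose assigned by enrolment order a true difference is possible, and then the change score is the unbiased estimate and ANCOVA is not. This objection stands and shapes the fix. Neither analysis removes calendar-time effects or unmeasured differences in patient mix.

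**The benefit is conditional.** A 1.2-pulse difference means that one dose has the full expected effect and the other none. Within the 20–30% range the difference is 0.4 pulses, and no analysis of 20 women detects it reliably. This also stands.

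**Covariates are often left to a separate analysis plan.** That would answer the point if the Protocol were silent. It instead has its own analysis section, and a synopsis row under that title, naming particular tests with no covariate.

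The choice of test for the before/after contrast within each dose is a separate question and is not argued here.

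**Conclusion.** The point holds as one of precision. The Protocol fixes only unpaired, covariate-free tests, although dose comparison is part of the primary objective and every outcome has a pre-injection value. If the tests are applied to each woman's reduction, the 95% CI for the dose contrast is wider than it need be: ANCOVA would narrow it by about 17%, 10% and 5% at ρ = 0.3, 0.5 and 0.7. For a 1.2-pulse difference the power gain is about 16, 9 and 2 points; for 0.4 pulses it is 2 to 3 points. Power and interval widths in pulses rest on an assumed SD of 1 pulse, and all the figures on assumed correlations, because the Protocol gives neither.

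It does not hold as a claim that the planned analysis ignores baseline, or that adjustment would make the two consecutive groups comparable. In a declared exploratory pilot the change is worth making, but the study does not fail without it.

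**What to change.** In the Statistical Analyses section (Description of Data and Primary Endpoint Analysis) and in the matching synopsis row, state the following:

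- The between-dose contrast on LH pulse frequency is a linear model for the post-injection value, with dose as factor and the woman's own 4-hour pre-injection pulse frequency as covariate. It is reported as an adjusted difference with 95% CI. Modelling the change instead gives the same adjusted difference.
- The same form is used for mean, basal and total LH (pre-injection value as covariate) and for the H8 hormones (H0 value as covariate).
- The unadjusted difference in change scores, with 95% CI, is reported beside it as a sensitivity analysis. The reason to give is that dose follows enrolment order and a noisy baseline covariate under-adjusts if the groups truly differ.
- The report will not claim that adjustment removes selection or calendar-time differences.

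The cost is wording only, with no new data or participants. The downsides are one residual degree of freedom (18 to 17), an assumed roughly linear relation to baseline, and possible residual bias if the groups truly differ.
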